## Abstract

**Background:**

Medical cannabis is now commonly prescribed for a range of chronic health conditions. Many medical cannabis products contain delta-9-tetrahydrocannabinol (THC), the intoxicating component in cannabis, though it is unclear whether these products produce impairment when used as prescribed and at therapeutic doses. With current Australian laws prohibiting driving with any amount of THC in one’s system, this trial aims to generate novel data on the impact of prescribed medical cannabis on real-world driving performance to inform road safety policy.

**Methods:**

This is a two-phase trial, with the first phase being a semi-naturalistic cohort study involving 72 patients with physician-diagnosed chronic pain, anxiety, or insomnia (*n* = 24 per group) who will complete repeated on-track driving assessments before and after consuming a standard dose of their medical cannabis prescription. The second phase is a randomised, placebo-controlled, double-blind, and crossover study involving 24 healthy participants who will complete the same repeated on-track driving assessments before and after consuming either alcohol (0.05% blood alcohol concentration) or placebo. Participants in both phases will also complete repeated cognitive assessments and assessments of subjective state and provide biological samples for analysis of cannabinoid (phase 1) and alcohol (phase 2) concentrations. The primary outcome measure is lateral vehicular control. Data will be analysed using a series of mixed-effect and generalised linear mixed models to assess changes in outcome measures over time.

**Trial registration numbers:**

ACTRN 17/09/2024 for 12624001118594 and 24/09/2024 for 12624001163594.

**Supplementary Information:**

The online version contains supplementary material available at 10.1186/s13063-026-09512-x.

## Introduction

### Background and rationale {6a}

Medical cannabis has been legal in Australia since November 2016. At the time of writing, Australia’s federal medicine and therapeutic regulatory agency—the Therapeutic Goods Administration (TGA)—had granted > 3.5 million approvals for access to medical cannabis. Of the >860,000 approvals for which product type and health indication data were available, approximately 80% were for Schedule 8 (S8) products containing THC. The remainder were for Schedule 4 (S4) products where cannabidiol (CBD) comprises > 98% of the total cannabinoid content. Nearly 50% of these approvals were for the treatment of chronic pain, with anxiety and sleep disorders (principally insomnia) the next most common indications for prescribing [1].

The intoxicating effects of THC have been extensively documented in laboratory investigations (e.g. [2–5]). When examining the magnitude and duration of drug effects on driving, ‘impairment’ is widely operationalised using the *standard deviation of lateral position* (SDLP), a measure of lane weaving and a proxy measure for general vehicular control. A recent meta-analysis concluded that THC-induced impairment in driving performance typically lasts for 3–8 h depending on the dose, route of administration, and frequency of cannabis use [6]. It is important to note that inhaled and oral cannabinoid products present unique pharmacokinetic profiles, which in turn produce variations in actual and perceived psychoactive drug effects, primarily due to differences in absorption, peak, and metabolic distribution [7, 8]. Inhaled cannabinoid products have a rapid onset of action and a relatively short window of peak effects, while oral products have a slower onset and longer duration of action [9].

Although prior acute drug administration research has established that cannabis can impair driving [10], the application of these findings to patients who are receiving long-term, stable treatment with medical cannabis is uncertain [11]. This is because previous research has primarily focused on investigating the effects of intentionally intoxicating doses of THC in healthy volunteers [6]. Under the Australian medical cannabis regulatory framework, patients are given a prescription for a specific cannabinoid product, much like how pharmaceutical medications are prescribed with pharmacy labels explicitly detailing dosage and frequency of use. This is a marked contrast to recreational cannabis, which is typically consumed via smoking and is often of unknown strength and quality. This key difference underscores the need for research that focuses on providing safety-relevant data specifically tailored to patient populations who are using medical cannabis as prescribed by a healthcare professional.

### Objectives {7}

The primary aim of this trial is to determine if and to what extent prescribed medical cannabis impacts on-track driving performance. This trial will also examine the effects of prescribed medical cannabis on cognitive function, subjective drug effects, and perceived driving ability. To provide a comparison to these findings, a secondary randomised, placebo-controlled trial will assess how a threshold legal dose of alcohol (0.05% blood alcohol concentration) impacts each of the same measures employed in phase 1. As BACs of ≤ 0.049% are legally permitted for drivers in Australia and numerous other countries, findings from phase 2 will provide an ecologically valid point of reference to findings obtained in phase 1.

### Trial design {8} and choice of comparators {6b}

We will conduct a two-phase trial to assess the effects of medical cannabis and alcohol on real-world driving performance. Phase 1 is a semi-naturalistic trial in which patients will complete driving assessments at two separate closed-circuit tracks (highway/urban driving environments) before and after consuming a standard dose of their prescribed cannabinoid medication. We decided not to institute a placebo control for patients as it was deemed unethical to withhold a patient’s treatment and because adequate blinding would be near impossible. In the absence of a placebo control for patients, we will implement an external control in the form of a secondary study (phase 2): a randomised, double-blind, placebo-controlled trial in which healthy volunteers will complete the exact same assessments at the same two tracks before and after consuming either alcohol (0.05% BAC) or placebo. Alcohol was chosen as the external control intervention for two reasons: (1) given the wide range of cannabinoid medications that we expect patients to be using, it would be impossible to select a ‘comparable’ dose or formulation for each participant and (2) because the dose to be administered is equivalent to the legal threshold for drivers in Australia (and numerous other countries) and thus has real-world relevance for road safety.

Phase 1 will involve 72 male and female patients (*n* = 36/*n* = 36) who are prescribed a THC-containing medical cannabis product (32 mg THC) to treat or manage chronic pain (*n* = 24), anxiety (*n* = 24), or insomnia (*n* = 24). These three conditions are the most common health indications for medical cannabis prescribing in Australia [1]. Patients will be further enrolled in a 1:1 ratio based on primary route of medical cannabis administration (inhaled or oral) and will complete assessments at different timepoints accordingly to account for differences in the pharmacokinetics and pharmacodynamics of inhaled and orally administered cannabinoid products [12]. This three-level stratification by gender, health condition, and route of administration will result in cell sizes of *n* = 6 (i.e. *n* = 6 males using an oral product for chronic pain), though this is for the purpose of maximising patient representation only and all patients will be treated as a single group for all primary statistical analyses. All patients will complete two testing days, including 1 day assessing highway driving ability and another day assessing urban driving skills. Treatments will be consumed by participants as prescribed by their physician in a supervised setting in the presence of a nurse.

Phase 2 (*healthy controls*) will involve 24 healthy male and female adults (*n* = 12/*n* = 12) who will complete a randomised, double-blind, placebo-controlled crossover trial to assess the effects of alcohol relative to placebo on real-world driving performance. Participants will complete two testing days per condition, 1 day assessing highway driving ability and another day assessing urban driving skills (i.e. four testing days total) during which they will receive alcohol (0.05% BAC) and placebo. Treatments will be administered orally (alcohol or placebo drink) using an established alcohol dosing formula in a supervised setting, with participants receiving treatments in a randomised and counterbalanced order.

## Methods: participants, interventions, and outcomes

### Study setting {9}

This trial will be conducted at Swinburne University of Technology and at two separate test sites: (1) METEC Driver Training facility and (2) Australian Automotive Research Centre (AARC). METEC is a driver training facility with 5 km of private closed roads and built-in traffic features including intersections, traffic lights, and roundabouts. AARC is an automotive proving ground with a 4.2-km-long two-lane highway circuit that follows the natural topography of the land and has a speed limit of 100 km/h. AARC is located in Wensleydale, approximately 2 h out of Melbourne. Over the course of the trial, and in both phases 1 and 2, participants will attend these two test sites for separate assessments of urban driving performance (METEC) and highway driving performance (AARC).

### Eligibility criteria {10}

#### Phase 1

For patients, inclusion criteria are as follows: (1) current medical cannabis prescription for chronic pain, anxiety, or insomnia persisting > 6 months, (2) on a stable dose of medical cannabis (≥ 3 months) with≥ 2 mg of THC/dose, (3) aged > 21 years, (4) in possession of a current and unrestricted Victorian driver licence, and (5) able to consume medical cannabis during the day as required for testing. Exclusion criteria are as follows: (1) On an unstable dose of medical cannabis or dose titrating, (2) unstable use of other medications that could impair driving, (3) unable to attend the test facilities for full-day testing sessions and stay overnight in a hotel for 2 nights, and (4) pregnant or lactating.

#### Phase 2

For healthy volunteers, inclusion criteria are as follows: (1) previous history of alcohol consumption in a single drinking session to an estimated BAC of 0.05% with no known adverse reaction [more than two standard drinks (female) or three standard drinks (male) on a single occasion], (2) under 100 kg (for weighted alcohol dose), (3) aged > 21 years and in possession of an unrestricted driver’s licence, and (4) oral fluid negative for all illicit drugs on the morning of test sessions. Exclusion criteria are as follows: (1) Use of cannabis > 1×/week; (2) AUDIT score (> 12) indicating problematic drinking; (3) use of any psychoactive medication that could impact driving; (4) current diagnosis of any Axis 1 mental health or substance use disorder; (5) taking any form of medication within 1 week of admission (except for routine medications to treat benign conditions); (6) unable to participate in scheduled visit, treatment plan, test, and other study procedures according to the protocol; (7) moderate-severe current depression (Beck Depression Inventory score of ≥ 20); (8) severe current anxiety (Beck Anxiety Inventory score of ≥ 16); (9) current participation in any other studies involving investigational or marketed products within 30 days prior to the screening visit; and (10) currently under administrative or legal supervision.

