Participants will be administered placebo or alcohol to achieve a target BAC of 0.05%, with an expected peak at 30–45-min post-ingestion. This will be achieved using an adjustable calculation based on the Widmark formula. Widmark’s formula states that one’s blood alcohol content is equal to the number of ounces of alcohol consumed, multiplied by a constant—for men by 3.75 and for women by 4.70—and then divided by that person’s weight. The formula is as follows: BAC = [alcohol consumed in grams/(body weight in grams × R)] × 100. For an average of 70-kg male person to achieve 0.05% BAC, this will require dosing of ~100 g of 40% alcohol or 3.7 standard drinks (30mL shots) with 201-g mixer orange juice (total drink 302 g). Placebo will be non-alcoholic vodka and orange juice, which we have effectively used to blind participants in previous studies. Non-alcoholic vodka is a clear, colourless liquid that is flavoured and formulated to mimic the taste and aroma of traditional vodka but contains no alcohol. Treatments will be prepared by the unblinded study nurse and given to participants in a stainless-steel mug with a lid and a straw to minimise potential unblinding during treatment administration. Allocation to treatment order (alcohol/placebo) will be randomised and counterbalanced according to a randomisation schedule held by the nurse and the study medical doctor. In the case of a serious adverse event occurring, emergency unblinding will be performed by the study nurse.

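### The published Phase 2 eligibility list does not exclude pregnant or lactating volunteers, although 12 women are to be given alcohol; the Phase 1 list does, and no reason is given for the difference

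*Protocol article*

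**What the plan says.** All references are to the protocol article.

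- **Eligibility criteria {10}, Phase 1.** There are four numbered exclusions. The last is "4) pregnant or lactating".
- **Eligibility criteria {10}, Phase 2.** There are four numbered inclusions and ten numbered exclusions. The final exclusion is "and (10) currently under administrative or legal supervision". The first inclusion sets a past-drinking requirement separately by sex: "more than two standard drinks (female) or three standard drinks (male) on a single occasion". The age rule is over 21 years, with no upper limit.
- **Trial design {8} and choice of comparators {6b}.** Phase 2 "will involve 24 healthy male and female adults (*n* = 12/*n* = 12"). On the test days: "Participants will complete two testing days per condition". On the exposure, the section speaks of four testing days "during which they will receive alcohol (0.05% BAC) and placebo".
- **Interventions {11} and allocation, Phase 2.** "Participants will be administered placebo or alcohol to achieve a target BAC of 0.05"%. The unblinded study nurse prepares the drinks.
- **Interventions {11} and allocation, Phase 1.** Patients take a standard dose of their own prescribed product, and the nurse checks it against the pharmacy label.

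**The concern.** The exclusion appears in the phase where participants take something they are already prescribed. It is absent from the phase where the trial itself prepares and gives the exposure to healthy people who gain no treatment benefit from it. The article offers no reason for the difference.

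What is at stake is participant safety. Eligibility is decided by the list, and a person screening volunteers against the Phase 2 list as printed has no stated ground for declining someone who is pregnant or breastfeeding. No estimate, error rate or sample size depends on this.

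**Working it through.** No power or sample-size figure bears on the point, so the check is a comparison of the two lists, followed by a count of who is exposed.

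**1. Is pregnancy or lactation named?**

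| | Inclusion items naming it | Exclusion items naming it |
|---|---|---|
| Phase 1 | 0 of 5 | 1 of 4 (the last item) |
| Phase 2 | 0 of 4 | 0 of 10 |

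The ten Phase 2 exclusions concern, in order: cannabis use, AUDIT score, psychoactive medication, Axis 1 or substance use disorder, recent medication of any kind, inability to take part, depression score, anxiety score, participation in other studies, and administrative or legal supervision.

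**2. Does another Phase 2 item cover it indirectly?** The nearest is exclusion (6), on inability to attend visits and complete the treatment and tests. A pregnant or breastfeeding volunteer can generally do those things, so the item does not exclude her. The description of participants as healthy does not settle the matter either: pregnancy is not ill health, and Phase 1 names it separately.

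**3. Does another section supply it?** The section Outcomes {12} and data collection methods {18a} describes a screening session with a medical history review and a questionnaire, and lists what the review collects. Pregnancy is not on that list for either phase. No other section shown mentions a pregnancy test, a contraception requirement or a lactation question for Phase 2.

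**4. Are women who could be pregnant or lactating eligible and exposed?** The age rule is over 21 with no upper limit, and the drinking criterion has a female threshold. The plan is 12 men + 12 women = 24. Because the design is a crossover, every participant receives alcohol, so all 12 women do.

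**5. How many alcohol days is that?** There are two test days per condition, so each woman has 2 alcohol days out of 4. Across all women, 12 × 2 = 24 planned alcohol days. This is the number of days to which the eligibility rule applies. It is not an estimate of how many would involve a pregnant or breastfeeding participant; the article gives no basis for one.

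**The case against.** The strongest reply is that a journal article condenses a longer protocol. All participants, not only Phase 1 patients, go through medical history review and a screening questionnaire. The printed topics of that review omit pregnancy even for Phase 1, where it must somehow be established, so the article evidently does not print every screening item. Fig. 1, the consent forms and the full protocol are not shown. A pregnancy question for Phase 2 could sit in any of them.

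That part stands, and it limits the conclusion to the published criteria. A reader might go further and infer that the trial has no such safeguard; the documents do not support that. Condensation does not remove the point, however. The article prints a long numbered Phase 2 list that reaches legal supervision and concurrent studies, and it names pregnancy and lactation in the shorter Phase 1 list of the same section. The point rests on two printed lists that differ, not on general silence.

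Three other inferences are tempting and should be resisted:

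- **That the two lists contradict each other.** They govern different populations and exposures, and many items properly differ; AUDIT and body weight, for example, appear only in Phase 2. The difference on pregnancy is an unexplained inconsistency, and no statement in the article is contradicted.
- **That 24 alcohol days are at risk.** As noted in the count, 24 is the women's planned total.
- **That the lack of an independent data monitoring committee makes the gap worse.** Nothing shows that such a committee would review individual eligibility. The article does describe fortnightly meetings with the sponsor, an internal steering committee, and a study nurse and doctor.

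The contrast with Phase 1 also needs one qualification. Phase 1 patients use their own product at the labelled dose, but some are asked to take it in the daytime when they normally would not, so Phase 1 dosing is not wholly undirected by the study. This softens the contrast without explaining why the safeguard is in one list only.

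**Conclusion.** The concern holds for the published eligibility criteria. Applied as written, the Phase 2 list would allow a pregnant or lactating volunteer to be enrolled and given alcohol, while the Phase 1 list excludes the same group. The rule as printed governs 12 of the 24 planned Phase 2 participants, each with two alcohol days. It should be corrected because the exposure is supplied by the trial, has no therapeutic purpose, and the repair is small.

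Confidence is high that the printed list omits the exclusion. Whether screening in practice covers it is unknown. If an unseen document does contain the exclusion, the published criteria misstate the eligibility rules and still need correcting. The point is one of safety and consistency, with no effect on power, the significance level or the analysis.

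**What to change.** Reconcile the two lists in Eligibility criteria {10}. Either carry the Phase 1 exclusion for pregnancy and lactation into the Phase 2 list and confirm it at the screening session that already exists, or state why the phases differ. The article does not say how Phase 1 establishes pregnancy or lactation status, so the method of confirmation needs to be written down.

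The Trial status section says recruitment began in October 2024 and is expected to finish in mid-2026. It does not give Phase 2 enrolment separately. The sponsor should therefore also check how any women already enrolled in Phase 2 were screened, and record the result.

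The cost is one line in the criteria, at most one item at screening, and a review of existing screening records. The downside is that a small number of volunteers would become ineligible. The planned sample size and analysis stay as they are.

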### Participant timeline {13}

#### Phase 1

In phase 1, patients will first complete a practice session and a baseline drive before completing two separate days of testing, including one test day at AARC and one test day at METEC. Due to the remote location of the AARC test track, participants will be transported by the research team and will stay in a hotel for 2 nights either side of the AARC test day. The test day schedule (see Fig. 1) will be identical for the two test days at AARC and METEC. Patients will complete three 20-min assessments of real-world driving performance over the course of each test day: one assessment (drive 1) prior to medical cannabis self-administration and two assessments (drives 2–3) after medical cannabis self-administration to assess acute effects. The timing of drives 2 and 3 will differ slightly depending on the route of administration to account for differences in cannabinoid pharmacokinetics and, by extension, the typical time course of expected behavioural effects (i.e. onset of effects, time to peak effects, and duration of effects).

**Fig. 1 Fig1:**
[figure not shown]
SPIRIT figure — schedule of enrolment, interventions, and assessments

For patients using oral products (*n* = 36), drive 1 will occur prior to medical cannabis self-administration, with drives 2 and 3 occurring 1.25 and 3 h after medical cannabis self-administration. For patients using inhaled products (*n* = 36), drive 1 will occur prior to medical cannabis self-administration, with drives 2 and 3 occurring 0.5 and 2.25 h after medical cannabis self-administration. Informed by prior work [13], drives 2 and 3 both fall within the potential window of impairment associated with inhaled and orally administered THC, with drive 2 corresponding to the expected period of peak effects, when impairment—if present—is likely to be greatest [14]. Blood and oral fluid samples will be collected immediately prior to each drive. An impairment assessment battery comprising cognitive testing and subjective drug effect questionnaires (see Outcomes {12}) will be administered immediately following each drive.

#### Phase 2

In phase 2, participants will first complete a practice session and a baseline drive before completing four separate days of testing, including two test days at AARC and two test days at METEC. Due to the remote location of the AARC test track, participants will be transported by the research team and will stay in a hotel for 2 nights before each of the two AARC test days before being transported back to Melbourne on the afternoon of the second AARC test day. Participants will then, in that same week, complete the two test days at METEC. Given the considerable logistical complexities associated with testing at remote locations, and to minimise potential dropouts, test days will be scheduled to occur back to back, meaning the washout period between test days will be minimal but within the expected metabolic elimination window for acute low doses of alcohol. As in phase 1, participants will complete three driving assessments within each test day, including a baseline drive in the morning (drive 1) followed by a second drive at the time of expected peak alcohol impairment (drive 2) and a third drive when impairment is expected to be subsiding (drive 3). The test day schedule (see Fig. 1) will be identical for each of these four testing days. The order in which participants receive alcohol and placebo at the two tracks will be randomised and counterbalanced.

